## Abstract

The mental health and related quality of life of runaway adolescents are global public health issues. As few intervention studies have considered the family contexts of runaway adolescents, we aimed to develop an intervention tailored specifically to the needs of this population using an Intervention Mapping protocol. First, a literature review and interviews with runaway adolescents and youth shelter workers were conducted to create a logic model of the problem. Second, the behavioral and environmental outcomes were set to adapt to stressful situations and enable families to become more resourceful in dealing with family adversity, based on the results of needs assessment. Performance objectives and changeable determinants were also created by reviewing the pertinent theories and studies. Third, theory- and evidence-based methods to influence changes in the determinants were identified. Fourth, we designed an eight-session family-based mental health program incorporating individual and family approaches for runaway adolescents. Fifth, we determined that mental health nurses at community mental health centers linked to youth shelters would serve as the program implementers. Finally, we planned a randomized controlled trial to evaluate the effects of our program on improving runaway adolescents’ mental health status and perceived family functioning.

## 1. Introduction

Runaway adolescents are at a high risk of mental health problems such as depression, post-traumatic stress disorder (PTSD), and suicidal ideation [1,2]. In addition, homeless adolescents have a higher rate of premature mortality due to suicide and substance abuse relative to the general adolescent population [3]. Previous studies indicated that runaway adolescents are not only prone to delinquent/criminal behavior but are also likely to become targets of sexual violence and prostitution [4,5].

Various factors contribute to the decision of an adolescent to run away from their home. In many cases, adolescents wish to escape an unsupportive, conflicted, or abusive home life or familial poverty [6,7]. In Korea, data from the Ministry of Gender Equality and Family indicate that family conflict was identified as the main motivator for running away by 70.0% of runaway adolescents [8]. In recent years, family conflict has tended to increase in frequency and complexity because of changes in family structures (e.g., divorce/separation) [9].

Family problems during childhood and adolescence are likely to lead to mental health problems. Particularly, family instability and conflict have important effects on a child’s mental health [9]. A previous study identified that family factors, including family instability and inappropriate parental attachment, can increase the morbidity associated with depression and alcohol abuse among runaway adolescents [10].

The traditional Korean family-centered culture prioritizes hierarchical order features in which authoritarian parents require children to comply with their demands. However, adolescents who have a perspective on Western individualism value individual freedom [11]. The authoritarian parenting style, which is against an adolescent’s expectations on autonomy, could lead to not only parent–adolescent conflicts [12] but also mental health problems among adolescents [13].

The capacities of psychological interventions such as art therapy [14], cognitive–behavioral therapy [15], motivational interviewing [16], and family therapy [17] to improve the mental health of runaway adolescents were investigated in previous studies. Although theoretically, these interventions were well-run programs, they were not developed systematically to reflect the real situations of runaway adolescents in Korea. Tailored and theory- and evidence-based interventions that consider the specific socio-cultural context are needed to improve the mental health of this population.

As family conflict is cited as the main reason for running away from home, programs without family engagement may be ineffective and lead to a chronic runaway status. In addition, because the levels of family functioning are correlated with mental health status among adolescents [18], family members should be included in interventions to improve the mental health of adolescents.

To address these concerns, we applied a systematic process to develop a theory- and evidence-based program with family engagement that would be tailored for runaway adolescents. This article describes the development of a family-based mental health program for runaway adolescents according to an Intervention Mapping (IM) protocol-based structured developmental process.

## 2. Materials and Methods

The IM protocol used in this study is a framework to guide the program planning process, which aids in developing theory- and evidence-based health promotion interventions, using a stepwise approach [19]. The IM protocol comprises six steps: (1) development of a logic model of the problem, (2) identification of program outcomes and objectives (logic model of change), (3) design of the program, (4) production of the program, (5) planning to implement the program, and (6) plan for evaluation [19]. The application of the IM protocol has advantages in promoting the development of tailored interventions to fit the needs of target groups and in establishing community-based interventions by allowing the participation of the key stakeholders in the program development process [20]. Several previous studies have used this protocol to develop mental health promotion programs [21,22,23].

### 2.1. Step 1. Logic Model of the Problem

In the first stage of the IM process, we identified the mental health problems and related quality of life issues faced by runaway adolescents, the behavioral and environmental factors related to these mental health and quality of life issues, and the determinants of behavioral and environmental factors. In addition, we described the context for the intervention and stated program goals. To complete these tasks, we used a comprehensive needs assessment including reviewing literature and theories, focus group interviews, and individual interviews.

To review findings from published literature for theory- and evidence-based answers to our questions, we conducted a comprehensive search of the published survey research, intervention studies, and literature reviews regarding the mental health problems and related quality of life issues experienced by runaway and homeless adolescents. In addition, we reviewed theories to understand mental health and family problems and to plan intervention.

The two focus group interviews involved convenience samples of eight shelter workers from two youth shelters providing residential shelter, food, and hygiene supplies to runaway youth. Youth shelter workers who are qualified social workers or youth counselors and who have substantial experience in counseling runaway adolescents were recruited. They discussed mental health and family relationship issues faced by runaway adolescents, the need for and feasibility of an intervention, and factors that should be considered. The approximately 1 h focus group interviews were conducted in meeting rooms at both shelters. For the individual interviews with adolescents, we used purposive sampling to ensure the inclusion of psychologically stable participants who would be able to discuss their experiences substantially. Five runaway adolescents from a youth shelter were recruited. They provided self-reported information about their mental health and family-related problems, the need for an intervention, and the type of help they want to get in an intervention. Each approximately 1 h individual interview was conducted in a counseling room at the youth shelter. All participants in the focus group and individual interviews signed a written informed consent. All interviews were audio-recorded and transcribed.

### 2.2. Step 2. Program Outcomes and Objectives-Logic Model of Change

In the second step of the protocol, we stated the expected behavioral and environmental outcomes based on the results of the needs assessment conducted in the first step. In addition, we specified performance objectives for the outcomes using theories as rationales. After selecting the important and changeable determinants of behavioral and environmental outcomes based on the results of our literature review conducted in step 1, we created a matrix of change objectives that the intervention would address.

### 2.3. Step 3. Program Design

In this third step, we selected the theory- and evidence-based change methods that we would use to influence the determinants of behavioral and environmental outcomes by reviewing the existing literature and theories of change. Subsequently, these change methods were translated into practical applications.

### 2.4. Step 4. Program Production

In the fourth step, we developed the scope and sequence of the program components, tools, and materials using information from steps one to three. We considered the program participants’ needs, feasibility, the context for the intervention including the population, setting, and community.

### 2.5. Step 5. Program Implementation Plan

In the fifth step, we aimed to prepare the adoption and implementation of the family-based mental health program by youth shelters in Korea considering the community context.

### 2.6. Step 6. Evaluation Plan

In the sixth stage, we aimed to develop an evaluation plan. Here, we specified effect evaluation questions which were corresponding with the program goal which was set based on the need’s assessment in step 1. We also determined the process evaluation indicators, the evaluation design, and methods of data collection and analyses.

## 3. Results

### 3.1. Step 1. Logic Model of the Problem

Through our literature review, we found that the mental health and related quality of life concerns of runaway adolescents comprise an important global public health problem. Compared to the general adolescent population, runaway and homeless adolescents were found to have higher rates of mental health problems such as conduct disorder, depression, anxiety, bipolar disorder, PTSD, suicidal ideation, and schizophrenia [1,6,24]. Regarding the quality of life, runaway adolescents also face a high risk of reduced emotional well-being [10], and dissatisfaction with family life [25].

Problematic alcohol use, risk behaviors [24,26], delinquency, criminal behavior, and school drop-out have been identified as behavioral factors associated with mental health problems and related quality of life issues [10,27].

Environmental factors can be classified as either interpersonal or community-level factors. At the interpersonal level, family factors such as poor communication, financial problems, poor psychological well-being of the parent or caregiver, poor emotional support at home [27], parental conflict, parental separation or divorce, parental alcohol abuse, and domestic violence [6,27] are associated with mental health problems and quality of life issues. Among runaway adolescents, relationships with peers and the presence of a caring adult are also related to mental health and quality of life issues [28]. At the community level, poor social connectedness, school and community environments, and economic opportunities can affect the mental health and quality of life of adolescents [28].

Poor self-esteem; a lack of adolescent resilience [28,29]; a lack of self-regulation, interpersonal, and/or problem-solving skills; a lack of self-efficacy [28]; poor parent–adolescent attachment [10]; a lack of family resilience; a lack of knowledge of parenting and adolescent development; parenting competency have all been identified as determinants of behavioral and environmental factors [28].

For two focus group interviews, five social workers and three youth counselors working at two youth shelters participated. They indicated that most of the runaway adolescents residing in youth shelters had experienced family-related difficulties such as parental divorce and family poverty, and were vulnerable to stress and mental health problems. They suggested the importance of providing an intervention targeted at improving the vulnerable mental health statuses and family functioning of adolescents. They also stated that an intervention should include promoting mutual understanding and emotional support between parents and adolescents, and having positive experiences with family through regular meetings. The focus groups explained that the return of adolescents to their homes may not be a possible outcome in some family cases because of financial difficulties and changes in the family structures due to parental divorce and remarriage. However, the focus groups suggested that improving the mental health status of adolescents and providing them with opportunities for positive experiences with family members are important in themselves, rather than as pathways to visible short-term outcomes such as the return of the adolescents to their homes.

Regarding the feasibility of an intervention, based on the focus group interviews, youth shelters strongly support the need for an intervention that aims to improve the mental health and family relationships among runaway adolescents. Shelters were willing to provide time and space required for the relevant intervention. In addition, the focus groups indicated that younger adolescents expressed a stronger will to reconcile with their family. However, the focus groups also had some concerns regarding encouraging adolescents’ parents to participate in an intervention owing to the parents’ lack of time and motivation attributed to their respective occupations.

The runaway adolescents who participated in individual interviews were likely to engage in risky and maladaptive behaviors in response to stress associated with family problems. They reported experiencing chronic family conflict and dissatisfaction with family life. They wanted individual mental health counseling and stated that their family members must have time to understand each other through an intervention.

Based on the results of this needs assessment, the program goal was set that mental health status and perceived family functioning are improved among runaway adolescents.

### 3.2. Step 2. Program Outcomes and Objectives—Logic Model of Change

The needs assessment in the first process resulted in the establishment of two expected outcomes for behavior and environment: Adaptation to stressful situations and family resilience as the capacity to be resourceful in dealing with family adversities.

While reviewing the relevant theories, we selected two theories providing rationales for performance objectives for the outcomes. The transactional model of stress and coping [30] was used as a basis for the behavioral outcome-related performance objectives, which were the use of effective coping strategies for stress and the seeking of help from social support networks in stressful situations. In addition, using the Walsh family resilience framework [31] as a rationale for the interpersonal environmental outcome-related performance objectives, we specified the performance objectives as the ability of family members to rebuild family relationships, communicate clearly and honestly, and collaborate to solve family problems.

Based on the results of our literature review conducted in step 1 of the IM process, attitudes, knowledge, skills, and self-efficacy were selected as determinants for the outcomes. Table 1 presents a matrix of the change objectives, which was constructed by crossing the performance objectives with the determinants and thus recording the change objectives.

### 3.3. Step 3. Program Design

We reviewed existing empirical evidence in the literature and theories of change to identify and choose theory- and evidence-based methods intended to influence changes in the determinants. As a result, we identified that motivational interviewing and cognitive reappraisal methods applied to the change objectives related to activating a positive attitude. Motivational interviewing to provide strength and motivation for positive changes [32] is used to facilitate changes in attitudes. According to the transactional model of stress and coping [30], a cognitive appraisal, which refers to the personal subjective interpretation of a situation and coping resources, influences an individual’s coping efforts and adaptation to a stressor. The ability to use cognitive reappraisal, which refers to the reframing of one’s thoughts to influence one’s responses to situations, could be a protective factor that enables an individual to adjust to stressful situations and reduce depressive symptoms [33]. To enhance knowledge, we derived the method of consciousness-raising from the transtheoretical model, which refers to increasing awareness about a specific problem behavior [34]. Skills training and guided practice methods were selected to enhance skills. Social modeling, emotional state improvement, and verbal persuasion were derived from Bandura’s theory [35] and selected to enhance self-efficacy. Table 2 lists the theory- and evidence-based methods and practical applications.

### 3.4. Step 4. Program Production

By integrating information from steps one to three, we developed a family-based mental health intervention for runaway adolescents aged 12–18 years who reside in youth shelters. Based on the results of needs assessment in step 1, we integrated the individual approach and family approach in the intervention. Considering the vulnerability of mental health among runaway adolescents, we consisted that adolescent individual sessions would precede family sessions. The focus group interviews conducted in step 1 revealed that most runaway adolescents residing in shelters experienced poverty, and adolescents’ parents lack time and motivation to participate in an intervention as they work to address financial difficulties. Therefore, considering the feasibility of the expected degree of family participation, an intervention format comprising four individual sessions with the adolescent and four subsequent family sessions in which the adolescents and their family members can engage together was considered appropriate. Hence, an eight-session program will be delivered in a shelter-based setting during a two-month period, and each session is expected to require approximately 60–90 min. Although the program was structured, the number of actual program sessions can be increased or decreased to accommodate the needs of adolescents and their families.

Based on the program plan from steps 2 and 3, the program components, tools, and materials were designed to ensure the achievement of the change objectives and effective operationalization of the methods and practical applications. In the first session, program engagement and motivational establishment through motivational interviewing techniques are the major emphases. In the second session, the cognitive reappraisal method is used to change the negative attitudes or beliefs influencing the adolescent’s negative emotions or behaviors on stressful events into positive attitudes or beliefs. In the third session, the participants are trained to cope effectively with stressful situations. The fourth session includes practical applications such as the provision of information about helpful resources, role-playing, mentor–mentee activities, and strong encouragement and support to encourage adolescents to seek help from social support networks in stressful situations.

The fifth to eighth sessions of the intervention will involve the family. The fifth session aims to improve family engagement and motivation for change. The sixth session includes the positive reframing of family adversities, education regarding differences between adolescents’ developmental needs and parental needs, and expressions of empathy and support to reconcile and rebuild the wounded family relationships. In the seventh session, family members are trained to communicate clearly and honestly. In the eighth session, family members identify family strengths, acquire problem-solving and decision-making skills, and practice these skills through family meetings to acquire family competence in collaborative problem-solving. Detailed information about the program components is presented in Table 3.

### 3.5. Step 5. Program Implementation Plan

We considered the community context to develop an implementation plan. Youth shelters refer runaway adolescents who need help with their mental health to community mental health centers, and adolescents residing in youth shelters are the subjects of the services provided by these centers. Therefore, to enable adoption, implementation, and maintenance of the developed program, the program implementers will comprise psychiatric and mental health nurses working at community mental health centers which were associated with youth shelters.

The psychiatric and mental health nurses at the community mental health centers will visit the youth shelters and deliver the program in counseling rooms. They will approach adolescents with cooperation from social workers at shelters and provide a program tailored to the characteristics of each adolescent.

The program implementers will receive education, training, and supervision by a nursing professor and principal investigator, and will provide the program to adolescents according to the program protocol. To maintain the quality of the services, the nursing professor and principal investigator will hold regular once-weekly meetings with the program implementers and youth shelter workers. Partnerships will be established between youth shelter workers and nurses from community mental health centers to enable cooperation.

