### 3.6. Step 6. Evaluation Plan

According to the program goal, which was set based on the need’s assessment in step 1, the hypotheses will test whether the mental health status and perceived family functioning improved in the intervention group relative to the comparison group. The primary outcome will be the effect of the program on mental health issues including depression, internalizing and externalizing behaviors, psychological distress, and suicidality among adolescents. These indicators were determined based on a review regarding outcome variables used in previous experimental studies of runaway and homeless adolescents. The secondary outcome will be the effect of the program on perceived family functioning among adolescents. The process evaluation should address the reach (percentage of the intended participants who used the program) and the dose of the intervention (average dose received by program participants). We will evaluate whether the needs of participants, as assessed in step 1, will be satisfied, and the new information and perspective generated in the evaluation process of the program will help us revise the previous steps in the IM process.

The effectiveness of the developed program will be evaluated in a randomized controlled trial (RCT). The participants will be divided into experimental and comparison groups via computer-generated random allocation. The participants that meet the following criteria will be included: runaway adolescents residing in youth shelters and 12–18 years of age. The exclusion criteria will be as follows: (1) adolescents diagnosed with an intellectual disability or specific learning disorder that can impair their ability to understand the intervention procedure and (2) those who are currently receiving other psychiatric treatments. In addition, family members currently receiving treatment for acute psychiatric symptoms will not be allowed to participate in the family sessions.

The participants’ data will be collected using self-administered questionnaire surveys, which will be completed individually in quiet counseling rooms to protect the participants’ confidentiality. The assessment time points will include the baseline (before the program) and immediately and 1 month after program completion.

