The data will be analyzed statistically using IBM SPSS Statistics for Windows, version 26.0 (IBM Corp., Armonk, NY, USA), and the intervention effects will be examined using a one-way repeated measure multivariate analysis of variance (MANOVA). A power analysis conducted using the G * Power program [36] indicated that a total sample of 211 subjects would be needed to detect a medium effect (*f* = 0.25) with 80% power using MANOVA at an alpha level of 0.05. Therefore, we will collect data from 118 participants each in the experimental and comparison groups (*N* = 236) to accommodate the expected attrition of 10% over the three-month period from the baseline assessment to the final evaluation.

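### The MANOVA and the sample size of 211 treat adolescents as independent, although program nurses form clusters in the experimental arm

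*Protocol article*

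**What the plan says.** All references are to the protocol article.

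- Delivery (section 3.5): "The psychiatric and mental health nurses at the community mental health centers will visit the youth shelters and deliver the program in counseling rooms". The format in section 3.4 is "four individual sessions with the adolescent and four subsequent family sessions in which the adolescents and their family members can engage together", so there are no adolescent groups.
- Allocation (section 3.6): "The participants will be divided into experimental and comparison groups via computer-generated random allocation". The unit is the adolescent, and eligibility covers "runaway adolescents residing in youth shelters and 12–18 years of age".
- Analysis (section 3.6): "the intervention effects will be examined using a one-way repeated measure multivariate analysis of variance (MANOVA"). No nurse or shelter term is named.
- Sample size (section 3.6): "a total sample of 211 subjects would be needed to detect a medium effect (*f* = 0.25) with 80% power using MANOVA at an alpha level"; the level used is 5%. The recruited number follows: "we will collect data from 118 participants each in the experimental and comparison groups (*N* = 236"), and the only reason given for the increase is "to accommodate the expected attrition of 10% over the three-month period from the baseline assessment to the final evaluation".

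The article does not give the number of nurses, their caseload, an ICC, the number of trial shelters or what the comparison group receives.

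**The concern.** A repeated-measures MANOVA models the correlation between one adolescent's measurements, over time and across outcomes. It takes different adolescents to be independent. In the experimental arm, adolescents seen by the same nurse share that nurse's skill, style and way of tailoring the sessions. The program, and with it the program nurse, belongs to one arm only, which makes this a partially nested design.

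If outcomes correlate within nurse, the experimental mean varies more than the model allows. The reported standard error is then too small, the test of no average program effect rejects too often, and the power calculation promises more than the design delivers. The sample size deserves attention before the trial starts, because a later analysis plan can change the model but cannot restore power once 236 have been recruited.

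**Working it through.** **Reproducing the 211.** Inputs from section 3.6: f = 0.25, alpha 0.05, power 80%, two groups. The number of responses is not stated for the power run. The primary outcome list gives five if internalizing and externalizing behaviors are counted separately. For a two-group MANOVA with p = 5, the noncentrality is N × f² and the degrees of freedom are p and N − p − 1.

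- N = 210: power 0.798.
- N = 211: noncentrality 211 × 0.0625 = 13.19, df 5 and 205, power 0.8003.

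A group-by-time calculation with six repeated measurements also gives 211. Both versions assume independent adolescents. Attrition: 211 / 0.9 = 234.4, so 235, or 236 for equal arms. Attrition therefore accounts for the whole increase, and nothing is left for clustering.

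**Effect of nurse clustering.** Assumptions, none of them in the article: k nurses with equal caseloads, one ICC for all outcomes, and nesting in the experimental arm only. Evaluable experimental adolescents: 118 × 0.9 ≈ 106.

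- Caseload m = 106 / k.
- Design effect in the experimental arm: DE = 1 + (m − 1) × ICC.
- Variance ratio of the group difference: v = (1 + DE) / 2.
- True type I error of a nominal 5% test of one outcome: 2 × (1 − Φ(1.96 / √v)).
- Power: the MANOVA above at N = 211, with noncentrality 13.19 / v.

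| Nurses | ICC | m | DE | v | True SE / reported SE | Type I error | Power |
|---|---|---|---|---|---|---|---|
| 20 | 0.01 | 5.3 | 1.04 | 1.02 | 1.01 | 5.2% | 79% |
| 10 | 0.05 | 10.6 | 1.48 | 1.24 | 1.11 | 7.8% | 70% |
| 5 | 0.10 | 21.2 | 3.02 | 2.01 | 1.42 | 16.7% | 46% |

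The middle row in full: DE = 1 + 9.6 × 0.05 = 1.48; v = 2.48 / 2 = 1.24; 1.96 / √1.24 = 1.76, which gives 0.078; noncentrality 13.19 / 1.24 = 10.64, which gives power 0.70.

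The power column keeps 205 denominator degrees of freedom. An analysis that respects a small number of nurses has fewer, so these powers are on the favourable side.

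**Check by simulation.** An unadjusted two-group test (212 adolescents, 8,000 runs, ICC 0.05) rejected in 13.1% of runs with 4 nurses, 9.3% with 8, 7.6% with 12 and 6.2% with 20. The formula gives 12.6%, 8.6%, 7.3% and 6.3%.

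**Shelters.** The same simulation with a shelter effect and no nurse effect covered 8 shelters with ICC 0.05 and 0.10, and 20 shelters with ICC 0.05. The type I error was 4.8% to 5.1% with simple allocation and 4.3% to 4.5% with allocation within shelter. There is no inflation.

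**The case against.** The strongest reply is that the size rests entirely on quantities the article does not give. With many nurses and a low ICC the effect is negligible, as the first row of the table shows. Several features could keep nurse differences small: a structured program, sessions held individually or with the adolescent's own family, common training and supervision, and weekly quality meetings. One-sided nesting is also an assumption. Section 3.5 says shelter residents are served by these same centers, so comparison adolescents may have some contact with center staff. Finally, the type I figures come from a single-outcome approximation and not from the planned MANOVA. All of this stands, and it is why the result is given as a range.

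It does not remove the point. The article names the model and fixes the sample size, and neither has room for a nurse effect.

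Two stronger readings are tempting. A reader might infer that living in the same shelter also narrows the error bars. It does not: allocation is by adolescent, so a common shelter effect falls on both arms, and chance imbalance between shelters is already part of the standard error. A reader might also infer that allocation ignores shelter, or that each nurse certainly treats many adolescents. The article says only that allocation is computer-generated, and blocks or strata may be described in a fuller protocol. A sizeable caseload is plausible with 118 adolescents at eight sessions each, but it is not stated.

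**Conclusion.** The point holds for nurses and not for shelters. The planned MANOVA and the 211 assume independent adolescents, while the delivery plan places the experimental arm in nurse clusters. Any positive within-nurse correlation makes the reported standard error too small and the stated 80% power too high.

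How far is open. Under the stated assumptions the consequence runs from practically nothing to a type I error more than three times the nominal 5% and power below one half. The middle case (10 nurses, ICC 0.05) costs about ten percentage points of power. The documents do not show which case applies, so they support a call to state the assumptions and model the nurse. They do not support a claim that the trial's error rate will be wrong by a given amount.

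**What to change.** 1. Record the delivering nurse for each experimental adolescent.
2. Replace the MANOVA as the primary analysis with a mixed model for the repeated measures that has a nurse random effect in the experimental arm only (partially nested) and small-sample degrees of freedom. This changes the named method; it is not an added term.
3. Restate the power for 236 recruited, with the planned number of nurses and a range of ICCs, for example 0.01 to 0.10.
4. Optionally, stratify allocation by shelter and adjust for it. This serves precision only.

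The trial is still to come, so recording the nurse and rewording the analysis cost little. The analysis becomes slightly more complex. The stated power falls, and not always slightly: at a variance ratio of 1.24 (about 10.6 evaluable adolescents per nurse, ICC 0.05), restoring 80% needs about 261 analysed, or 261 / 0.9 = 290 recruited against the planned 236. The alternative is to keep 236 and report the lower power openly.
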